## Abstract

**Background:**

Children in Sub-Saharan Africa are burdened by significant unmet mental health needs. Across the region, high rates of poverty, HIV/AIDS, food insecurity, stigma, and an inadequate health safety net system exacerbate serious child behavioral health needs and impede an effective response. Disruptive behavioral disorders are particularly concerning as they persist through adolescence and adulthood. Hence, addressing the context-specific social influences on child behavioral health is critical given that children in the region comprise more than half of the total regional population. Against this backdrop, this study protocol describes a randomized clinical trial that will examine the mechanisms by which economic empowerment and family strengthening interventions targeting social, familial, and context-specific drivers affect the mental health of children in Uganda.

**Methods:**

The study uses an experimental, longitudinal design across 30 cluster-randomized primary schools to compare single and combination intervention options; influences of economic empowerment and family strengthening on economic, perceptual, and functioning mediators; and context-specific moderators. The study will be conducted with 900 Ugandan children in mid-upper primary school (10–14 years). The three study conditions (*n* = 300 each) are: (1) economic empowerment only (EE only), (2) multiple family group-based family strengthening only (MFG-based FS only), and (3) combined EE + MFG-based FS. The interventions will be provided for 12 months; and assessments will occur at baseline, 12, 24, and 36 months.

**Conclusion:**

Children in Sub-Saharan Africa are burdened by significant unmet mental health needs, including disruptive behavior disorders that persist through adolescence and adulthood if left untreated. The proposed study will examine the mechanisms by which economic empowerment and family strengthening interventions targeting social, familial and context-specific drivers affect the mental health of children in mid-upper primary schools in Uganda. Findings from this study can inform group, community, and population approaches that are needed for scalable solutions to address the social drivers negatively impacting child behavioral health in low-resource settings, including in Sub-Saharan Africa.

**Clinical trial registration:**

[https://clinicaltrials.gov/], identifier [NCT053 68714].

## Introduction

Children in Sub-Saharan Africa (SSA) experience a significant rate of unmet mental health needs (1, 2). According to a recent systematic review, 1 in 7 children in the region struggle with a serious mental health issue (3). Across SSA, high rates of poverty, food insecurity, stigma, and an insufficient health safety net system further intensify serious child behavioral health needs and hinder an effective response. Moreover, higher rates of child behavioral challenges in the SSA region, a region heavily impacted by HIV/AIDS, have been found among children impacted by HIV/AIDS (1, 4–10).

Child disruptive behavior disorders (DBDs) are particularly concerning as they can persist through adolescence and adulthood, if not addressed in a timely manner. DBDs are also associated with poor physical health and interpersonal challenges in adulthood (4–7). Hence, the importance of addressing the context-specific social influences on child behavioral health, as well as the magnitude of the task cannot be overstated, given that children in SSA comprise more than half of the total regional population (1).

If children’s needs are to be met in SSA, then: (1) implementing interventions designed and tested in SSA, and which mobilize resources within existing child-focused institutions (families and schools) is critical (8–10); (2) combined interventions that simultaneously target SSA-specific influences on child behavioral health (family financial stability and culturally based parenting), and can be delivered in collaboration with child/family-serving community settings (schools and faith-based and financial institutions) are necessary (9); and (3) group, community, and population approaches to child behavioral health are needed to drive scalable solutions (9, 11, 12).

Savings-led economic empowerment interventions (13–25) have demonstrated to be efficacious in addressing the myriad of needs presented by children living in poverty- and AIDS-impacted communities in SSA, including improvement in mental health functioning (15, 17, 19, 26). Economic empowerment interventions directly target family financial stability and investment in the protection of children *via*: (1) incentivized matched Child Development Accounts (CDAs), (2) financial literacy training (FLT) and income-generating activities (IGAs) for families, and (3) mentorship. In addition, family strengthening interventions can positively impact CBH in SSA (27–29). Although scientists continue to disentangle the effects of culture and context on parenting and childhood DBDs across SSA, it is well recognized that the basic principles (e.g., behavioral supports, parent–child relationships, and involvement) underlying effective parenting practices are considered cross-culturally robust and play a critical role in child behavioral health (30–32). The multiple family group (MFG)-based family strengthening intervention to be tested in this study has shown to be efficacious in reducing oppositional defiant disorder symptoms and impaired functioning relative to usual care at 16 weeks (post-intervention) (33). The results also showed improved familial and peer relationships as well as better behavioral outcomes among children.

Against this backdrop, guided by Social Action (34), Asset (35, 36), and Family Systems (37) theories, the proposed study examines the mechanisms by which economic empowerment and family strengthening interventions targeting social, familial and_context-specific drivers affect the CBH of Ugandan children in mid-upper primary school (10–14 years). Specifically, the study uses an experimental, longitudinal design with three active study conditions across 30 cluster-randomized primary schools to compare single and combination intervention options; influences of economic empowerment and family strengthening interventions on economic, perceptual, and functioning mediators; and context-specific moderators. The study has the following specific aims:

Aim 1: Examine the impact of economic empowerment (EE only), multiple family group-based family strengthening (MFG-based FS only), and combined EE + MFG-based FS on children’s DBD symptoms and behavioral functioning;

Aim 2: Test the influence of EE only, MFG-based FS only, and combined EE + MFG-based FS on family financial stability (e.g., food and housing stability, material assets, and savings), parenting and protective family processes (e.g., family organization, caregiver/child interaction, cohesion, and support) and perceptions related to help seeking (e.g., stigma) on child behavioral health and functioning; and assess whether these change mechanism mediate intervention effects on DBD symptoms and behavioral functioning, and explore moderation by context-specific moderators of intervention effects;

Aim 3: Qualitatively examine participants’ experiences with each intervention arm.

## Background

A recent systematic review estimated that 1 in 7 children in SSA may struggle with a serious mental health issue (3). The WHO estimates prevalence rates may be even higher (20%) (38). In Uganda, 12–29% of children presented mental health symptoms when screened in primary care clinics (39, 40). Similarly, Nalunga (41) found that 1 in 5 Ugandan adolescents experienced a serious mental health challenge. In SSA, high rates of poverty, housing and food instability, effects of HIV and other health threats, and an inadequate health system exacerbate the prevalence of mental health needs and impede an adequate response.

Youth disruptive behavioral disorders (DBDs), including in SSA, are a particularly serious concern as they persist through adolescence and adulthood (4–7). The prevalence of DBDs in LMICs, including six SSA countries varies from 12 to 33% (3, 42–46). In a recent study with 2,434 school-going children in southwest Uganda screened for disruptive behaviors, 6% scored positive on oppositional defiant disorder and 2% scored positive on conduct disorder. In addition, 9.61% were reported to have elevated symptoms of oppositional defiant disorder (47). Children orphaned by AIDS or living with an HIV-infected parent were found to exhibit either an emerging or clinically serious DBD (13, 48–54). These prevalence rates translate into staggering numbers of children in need with child-serving systems not equipped to meet their needs (1, 4). For instance, in Uganda, there are only five child and adolescent psychiatrists, who are all located in urban tertiary care centers (55).

Disruptive behavior disorders are chronic, impairing, and costly mental health problems. When untreated, they can put youth at increased risk for future school drop-out, social impairment, substance use, delinquency, incarceration, criminal behaviors, unemployment, and premature death (4–7, 56–62).

### Risk factors for disruptive behavior disorders

Risk factors for an increased incidence of childhood DBDs include poverty, harsh parenting, poor caregiver–child relationships, large family size, stress, and the death of one or both parents (3, 31, 42, 43, 46). Given the negative consequences associated with childhood DBDs, it is critical that effective and scalable solutions that recognize the challenges facing most SSA countries are discovered. Specifically in Uganda, children constitute about half (56%) of the total population (compared to 20% in the US) (63) and simultaneously experience multiple physical, mental health, and academic challenges (55, 63). Ugandan children reside in communities that experience high rates of chronic poverty (38%), domestic violence (30%), physical violence toward children (80%), depression (33–39%), malaria (70–80%), and HIV/AIDS (6%) (4, 55, 64–67), and with a high number of orphans (4, 63). In addition, in order to effectively improve the mental health of the child population in SSA, one must address mental health stigma (68, 69), skepticism toward professional mental health support (2, 70–72), the large number of youth orphaned by HIV and other health epidemics, and limited economic opportunities (15, 19, 25, 73–80). Thus, culturally and contextually adapted family strengthening interventions that bolster SSA-specific family processes and parenting specific to SSA are needed to effectively address childhood DBDs. The group-delivered family strengthening interventions are specifically designed to target DBDs for youth whose families struggle with poverty and stress in the US and in SSA (27, 28, 81–83).

### Family strengthening interventions targeting disruptive behavior disorders

Positive behavioral supports, effective behavioral management, caregiver–child relationship, and caregiver involvement in a child’s life are critical to healthy child development regardless of families’ cultural or ethnic background. Several DBD-focused evidence-based practices (EBPs) are designed to enhance parenting skills (84–87) using behavioral practice, modeling, coaching, goal setting, family communication, and building on family strengths (2, 88–90).

Guided by Social Action (34) and Family Systems (37) theories, the family strengthening intervention recognizes the link between protective parenting practices and family processes, as well as contextual circumstances and supports in order to address childhood DBDs. Kazdin and Whitley (91) described how specific family factors associated with poverty (e.g., stress) may undermine parenting (e.g., family organization, discipline practices, family connectedness, support, and communication) and contribute to serious child behavior problems (15, 25, 80, 92–94). In collaboration with parents and service providers in the US, a MFG delivered family strengthening intervention was developed and guided by a protocol that encouraged transparency of the evidence base for families and provided an “easy to remember” means of organizing existing science for lay facilitators. Specifically, 4 broad conceptual categories are targeted at the family level for family strengthening (4Rs): Rules, Responsibility, Relationships, and Respectful communication. Stress and Social (2Ss) support were added given that these are factors that impact service engagement and outcomes among children raised within poverty-impacted families (39, 84, 92, 95–99). The 4Rs and 2Ss Family Strengthening Program is listed on the National Registry of Evidence-based Practices (100).

These components are embedded within the family strengthening intervention to be tested in the current study. Referred to as the 4Rs and 2Ss Family Strengthening program in the US, the AmaQhawe Family Program in South Africa (Strong Family in Zulu), and the Amaka Amasanyufu program in Uganda (Happy Families in Luganda), this intervention has been tested first in developed countries and in similar high poverty and high-stress communities in SSA – one of the few that is supported by data from SSA (27, 101). Specifically in Uganda, where the intervention was tested with children experiencing behavioral challenges and their families in a region heavily impacted by poverty and HIV, the results showed that the intervention was efficacious in reducing oppositional defiant disorder symptoms and impaired functioning relative to usual care at 16 weeks (post-intervention) (33). The results also showed improved familial and peer relationships as well as better behavioral outcomes among children.

### Economic empowerment interventions

Given the persistent threats associated with poverty, without attention to family economic stability, even with family strengthening interventions, families may not be able to fulfill their mental health promoting roles for children. Poverty affects families’ ability to physically care for children as well as family stability, functioning, and psychosocial wellbeing, thus constituting an important influence on child mental health. Studies have shown that family economic stability influences the quality of family relationships, where poverty negatively impacts caregiver–child communication and involvement (76, 102–104). In fact, the lack of material resources across contexts has been shown to undermine parents’ ability to foster children’s emotional and behavioral wellbeing by creating tense day-to-day interactions and compromising adult caregivers’ ability to positively direct children’s behavior (74, 105–111).

Studies have documented that the stresses and strains associated with poverty also can lower the connectedness between a child and his/her primary caregiver, which then predicts childhood mental health and functioning across domains (74, 105–111). Families who spend disproportionate time on material acquisition and survival have less frequent parent/child communication, thus driving poorer child psychological adjustment (74, 105–111). Moreover, families play a critical role in child development (including adolescence) and relatedly in any potential intervention designed to address the needs of young people (including the age group targeted by the proposed Suubi4StrongerFamilies intervention) (112). Indeed, the connectedness between a child and his/her primary caregiver can predict mental health functioning and overall child adjustment (113–115).

The parental role can provide an important protective factor for children who see themselves as connected to their families, and are thus less likely to suffer from mental disorders (115–121). Thus, particularly in resource-limited settings, providing families with economic opportunities can either maximize the benefits of family strengthening interventions or potentially eliminate the need for family strengthening entirely as economic empowerment diminishes the burden on families to rear children and support their behavioral success.

Economic empowerment interventions are guided by Asset theory (35, 122) according to which asset ownership can lead to many benefits, including expectations for more resources in the future, optimistic thinking, feelings of safety and security (123), and future planning (124). Asset building refers to efforts that allow people with limited economic opportunities to acquire and accumulate long-term assets (125). It is viewed as a critical strategy to reduce poverty, positively impact attitudes and behaviors, and improve psychosocial functioning (36, 125–127). Asset theory is consistent with other behavioral and psychosocial theories, including Bandura’s Social Cognitive Theory (128) and the Theory of Reasoned Action (129–134).

The economic empowerment intervention proposed in the current study draws on now robust evidence of the positive impact of savings-led economic empowerment approaches to improving family financial stability. Although similar to conditional cash transfers, which have become popular in the social development field and seek to enable families to meet their basic needs while incentivizing child behavioral protection (135–139), matched savings accounts proposed in this study go beyond that by underscoring long-term investment and promote life-long financial inclusion by developing savings habits and establishing partnerships among the participating families, financial institutions and the intervention program. For the proposed study, a CDA will be used, where savings are housed at a local bank and deposits made by the family are matched by the intervention to encourage savings. CDAs yield positive effects, including a greater sense of security, self-confidence, and future orientation (15, 16, 19, 74, 76, 77, 80, 140). CDAs also provide children and families with basic financial education, introduce them to formal financial institutions, and incentivize them to save small amounts by matching their deposits.

Given these complex mechanisms and pathways through which any given intervention may impact the overall mental health and psychosocial functioning of young people in SSA, investments in combination multi-level interventions are critical to providing an interdisciplinary, multi-level response desperately needed to improve child behavioral health and functioning in a way that single interventions alone have not yet sustainably been able to do. Thus, the current study examines the mechanisms by which economic empowerment and family strengthening interventions targeting social, familial, and context-specific drivers affect child behavioral health.

## Methods

This is a three-arm randomized control trial that will evaluate the mechanisms by which Economic Empowerment and Family Strengthening interventions targeting social, familial, and context-specific drivers affect child behavioral health (see Figure 1). More specifically, this study examines the direct impact of EE, FS, and combined EE + MFG-based FS on children’s DBD symptoms and behavioral functioning. In addition, the study examines the influence of EE, FS, and combined EE + MFG-based FS on family financial stability (e.g., food and housing stability, material assets, and savings), parenting, and protective family processes (e.g., family organization, caregiver/child interaction, discipline practices, cohesion, and support) and perceptions related to help-seeking (e.g., stigma) on child behavioral health and functioning. Finally, the study explores context-specific moderators of intervention effects (e.g., family circumstances, including deaths of adult caregivers, combined family structures, connection to community, and religious and cultural resources).

**FIGURE 1 F1:**
[figure not shown]
Study design.

We expect to involve 900 youths aged 10–14 years in primary schools, grades 5 through 7, and their adult caregivers (900) in Uganda. The selected schools will be randomized to three study conditions: (1) EE only condition with a 1:2 saving incentive match—for educational purposes and microenterprise development (*n* = 300 participants; *n* = 10 schools); (2) MFG-based FS only condition (*n* = 300 participants; *n* = 10 schools; (3) combined EE + MFG-based FS condition (*n* = 300 participants; *n* = 10 schools). There will be four data points, these include baseline (pre-test), 12, 24, and 36 months post intervention.

### Study setting

According to the Ministry of Health’s most recent estimates, the HIV prevalence among adults (15–49 years) in Uganda is 5.4%, and 98,000 children (ages 0–14) are living with HIV (141). The study will be conducted with 900 youth aged 10–14 from 30 primary schools in five districts of Masaka, Rakai, Kyotera, Lwengo, and Kalungu in the Greater Masaka region, with 9.2% HIV prevalence rate (as opposed to 5.4% nationally) (141).

### Randomization

As in our prior studies (142, 143), stratified randomization of schools to conditions will be used, with schools stratified into four strata based on two variables: (1) student population size (medium size vs. large), and (2) geographical location (rural vs. urban), to ensure balance on those variables. The restricted randomization technique of Hayes and Moulton (142) will be used within the four strata to assure overall school balance across the three groups. Each of the 30 schools will be randomly assigned to one of the three study conditions and all selected students from a particular school will receive the same intervention (to reduce contamination). More specifically, 10 schools will be randomly assigned to receive an EE alone (*n* = 300 students), 10 to MFG-based FS intervention (*n* = 300 students), and the final 10 to the combined EE + MFG-based FS intervention condition (*n* = 300 students).

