### Data analysis

#### Data quality assurance, initial analyses, and missing data

We will use MIS IDA Q (175) to check for data entry errors and missing values (175). Frequencies and measures of central tendency and variability will characterize the sample. We will address incomplete data with direct maximum likelihood (ML) and multiple imputation (MI) (175). Program code and results will be documented and archived to enable future access and dissemination.

#### Primary analyses for Aim 1

We hypothesize that: (1) H1a: Relative to participants in the MFG-based FS only group, participants in the combined EE + MFG-based FS will have lower mean levels of oppositional defiant disorders and functional impairment following the intervention; and (2) H1b: Relative to participants in the EE only group, participants in the combined EE + MFG-based FS group will have lower mean levels of oppositional defiant disorders and functional impairment following the intervention. To test hypotheses H1a–H1b, we will fit three-level linear mixed models (LMMs) to (1) the Iowa Connors measure of oppositional defiant disorder and (2) the Impairment Rating Scale (IRS). Each of these two models will include fixed effects for study arm, time, and their interaction. We will use random intercepts for School ID to account for clustering of persons within schools and include random intercepts, random slopes, and their covariance for person ID to account for clustering of repeated measurements within persons. To test H1a–H1b for each outcome we will perform two time-averaged comparisons of repeatedly measured observations across study arms to examine intervention effects over the duration of the post-intervention study period. Because two comparisons among the study arms will be evaluated per outcome, alpha (α) will be set at 0.05/2 = 0.025 for each of these planned comparisons.

#### Secondary exploratory analysis for Aim 1

While we do not have a formal hypothesis regarding the superiority of EE-only to MFG-based FS-only, when we fit the LMMs described above we will also explore whether EE only is superior to MFG-based FS only or vice versa. This exploratory comparison will be tested at α = 0.05.

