#### Primary analyses for Aim 2: Evaluating the effects of the intervention on mechanisms of change

We hypothesize that: (1) H2a: Relative to participants in the MFG-based FS only group, participants in the combined EE + MFG-based FS group will have higher levels of family financial stability, parenting and protective family processes, and perceptions related to help seeking following the intervention; and (2) H2b: Relative to participants in the EE only group, participants in the combined EE + MFG-based FS group will have higher levels of family financial stability, parenting and protective family processes, and perceptions related to help seeking following the intervention. To test hypotheses H2a–H2b for mechanisms of change (e.g., asset ownership scale and food security) we will fit LMMs using the same fixed effects (study arm, time, and study arm-by-time interaction) and random effects for the school (random intercepts) and person levels (random intercepts, random slopes, and their covariance) as in the proposed H1 analyses described above. To test H2a–H2b we will perform two time-averaged comparisons of repeatedly measured observations of financial stability, parenting and protective family processes, and perceptions related to help seeking at α = 0.025 per comparison.

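### Schools are randomised within four size-by-location strata, but the stated H1 and H2 models have no stratum term; if size and location predict outcome, the arm comparisons are conservative

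*Protocol article*

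**What the plan says.** **Design.** Under Randomization, the protocol article has "schools stratified into four strata based on two variables: (1) student population size (medium size vs. large), and (2) geographical location (rural vs. urban". The restricted technique "will be used within the four strata to assure overall school balance across the three groups". The school is the unit of allocation: "Each of the 30 schools will be randomly assigned to one of the three study conditions", ten schools to each.

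**Aim 1 analysis.** Under Primary analyses for Aim 1, the text for the two outcome models reads "Each of these two models will include fixed effects for study arm, time, and their interaction". The random part is given in detail. On schools it says "We will use random intercepts for School ID to account for clustering of persons within schools"; at person level there are intercepts, slopes and their covariance. The hypotheses are tested as follows: "we will perform two time-averaged comparisons of repeatedly measured observations across study arms", and "alpha (α) will be set at 0.05/2 = 0.025 for each of these planned comparisons".

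**Aim 2 analysis.** For the mechanisms of change, "we will fit LMMs using the same fixed effects (study arm, time, and study arm-by-time interaction", with the same random effects.

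**Elsewhere.** The moderation section adds sex, orphanhood, community connection and religious or cultural resources. No section brings school size, location or stratum into a model.

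**The concern.** Balancing the arms within strata takes between-stratum differences out of the arm contrast: each arm holds a similar mix of large, medium, rural and urban schools. The estimate therefore varies less over repeated randomisations than under simple randomisation. A model without stratum terms does not know this. It assigns the differences between strata to the school random intercept and charges them to the standard error of the arm contrast. The reported standard error then exceeds the true sampling variability, the test rejects less often than its nominal 0.025, and power is lost.

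This matters because there are only ten schools per arm, both primary contrasts compare two active conditions, and the Statistical power analysis section claims 80% power only down to d = 0.24–0.29. A test more conservative than intended could miss a real added benefit of the combined arm.

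**Working it through.** **Inputs from the article.** 30 schools, 10 per arm (Randomization). After 20% attrition, 720 children in 30 schools, which is 720/30 = 24 per school; three repeated assessments; power 0.80 (Statistical power analysis). Alpha 0.025 per contrast (Primary analyses for Aim 1), taken as two-sided.

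**Assumptions, because the article gives no figure.** School ICC; within-person correlation rho = 0.5; share R² of between-school variance explained by the strata; stratum sizes.

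**Step 1: variance of a time-averaged contrast between two arms** (unit outcome variance).

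Var = (2/10) × [ICC + (rho − ICC)/24 + (1 − rho)/72]

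Multiplying the bracket by 72 with rho = 0.5 gives a factor f = 2 + 72·ICC − 3·ICC. With strata in the model only the school term shrinks:

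f(R²) = 2 + 72·ICC·(1 − R²) − 3·ICC, and the standard-error ratio is √[f(R²)/f(0)].

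**Step 2: the article's own figure.** Detectable d = (2.241 + 0.842) × √[(2/10) × f/72]. At rho = 0.5 this gives 0.267 at ICC 0.01 and 0.299 at ICC 0.02; at rho = 0.3 it gives 0.246 and 0.281. The printed range of 0.24–0.29 is therefore attainable, but no unique pair of inputs can be recovered from it.

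**Step 3: effect of adding the strata** (rho = 0.5).

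| ICC | R² | f without strata | f with strata | SE ratio | SE reduction |
|---|---|---|---|---|---|
| 0.02 | 0% | 3.38 | 3.38 | 1.000 | nil |
| 0.02 | 20% | 3.38 | 3.092 | 0.956 | 4% |
| 0.02 | 40% | 3.38 | 2.804 | 0.911 | 9% |
| 0.05 | 0% | 5.45 | 5.45 | 1.000 | nil |
| 0.05 | 20% | 5.45 | 4.73 | 0.932 | 7% |
| 0.05 | 40% | 5.45 | 4.01 | 0.858 | 14% |

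**Step 4: simulation of school means.** Assumed strata of 9, 9, 6 and 6 schools, arms balanced within each, rho 0.5, two-sided alpha 0.025.

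At ICC 0.02 the model without strata reports a mean standard error of 0.097. The true standard deviation of the estimate is 0.091 at R² 25% and 0.085 at R² 50%. Actual type I error is about 0.018 and 0.012; with stratum terms it is 0.024 and 0.026.

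Power at d = 0.29, the upper end of the article's range:

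| ICC | R² | Without strata | With strata |
|---|---|---|---|
| 0.01 | 0% | 0.83 | 0.83 |
| 0.01 | 20% | 0.83 | 0.85 |
| 0.02 | 0% | 0.73 | 0.73 |
| 0.02 | 10% | 0.74 | 0.75 |
| 0.02 | 20% | 0.74 | 0.77 |
| 0.02 | 40% | 0.74 | 0.81 |
| 0.05 | 10% | 0.51 | 0.53 |
| 0.05 | 40% | 0.49 | 0.64 |

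**Step 5: cost.** Three stratum terms reduce school-level degrees of freedom from 27 to 24. The critical t at two-sided 0.025 goes from 2.373 to 2.391, a ratio of 1.007.

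**The case against.** **The article condenses a longer plan.** Covariate adjustment is often left to an analysis plan, and saying that a model includes certain effects does not say it includes only those. This has some force, but the specification reaches down to the intercept–slope covariance, and the Aim 2 text restates the fixed effects as a bracketed list. A model described that fully and at odds with the allocation scheme is a stated choice, and a later plan that followed it would carry the mismatch forward.

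**The loss is conditional.** This stands. Nothing in the article shows that school size or location predicts caregiver-rated behaviour or impairment, and the stated purpose of stratifying is balance. Stratum sizes are not given either; where a stratum does not divide by three, balance is only approximate and less variance is removed. With R² at 10% or below, power changes by only about 0–3 points.

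**The contrast might remove stable differences anyway.** If the time-averaged comparison were taken as change from baseline, constant stratum differences would cancel. The text speaks of the post-intervention period, and the power calculation uses three assessments, so a post-intervention contrast is the more natural reading. This remains a caveat.

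**Stronger readings.** A reader might infer that the planned standard errors are certainly inflated, or that the trial's results would be biased. The first needs prognostic strata, which the documents do not establish. The second is wrong: the omission pushes the test in the conservative direction and leaves the estimates unbiased. A reader might also want every variable used in the restricted randomisation added to the model. The article names none beyond size and location, so that request has no visible basis.

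**Conclusion.** The mismatch between design and stated model is in the text, and it should be corrected. Its consequence is possible loss of precision: the intervals may be too wide and the tests conservative. The standard-error reduction on offer runs from about nil to 4–9% at ICC 0.02 and to 7–14% at ICC 0.05, the upper ranges requiring strata that explain 20–40% of between-school variance. These figures rest on 24 children per school, three follow-ups, a within-person correlation of 0.5 and near-exact balance within strata. ICC and R² are assumptions throughout. The case for change does not depend on the larger values: the simulations show no material power cost from adjustment when the strata are uninformative, and some gain when they are not.

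**What to change.** In the Aim 1 model description, and by reference in the Aim 2 one, state that every H1 and H2 mixed model includes the four-level randomisation stratum (school size, location and their interaction) as a fixed effect. Allow main effects of size and location only, if a stratum turns out to be very sparse, and write that rule down in advance.

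The cost is one sentence and no new data, since size and location must be known in order to randomise. It uses at most three of 27 school-level degrees of freedom (two with main effects only). If the strata carry no information, intervals widen by about 0.7%.
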